#### **Pre-defined exploratory endpoints:**

*The following endpoints will be examined to assess various aspects of SNAQ app use in terms of usefulness, nutrition literacy, psychosocial, and behavioral impact. Pre-specified exploratory endpoints will be reported as point estimates with 95% confidence intervals (unadjusted for multiple testing), so definite inferences cannot be made regarding those endpoints.*

#### **Usability and patient reported outcomes:**

- Engagement with the SNAQ app in the 3-week follow-up period (frequency of use)
- Technology satisfaction (assessed using a self-designed feedback questionnaire) and psychometric questionnaires

#### **Nutrition literacy**

- Carbohydrate estimation skills (absolute and relative errors from the carbohydrate quiz)

### **Meal management behavior**

- Meal patterns (Timing of meals, macronutrient content of meals)
- Daily number of manual boluses,
- Total daily Insulin dose (basal dose, bolus dose and total dose)

### **Glucose control**

In addition to the above mentioned primary and secondary outcomes, several further metrics of glucose control will be analysed, including the following: % time 10.1-13.9 mmol/L, %time >13.9 mmol/L, % time 3.0-3.9 mmol/L, %time <3.0 mmol/L, mean glucose, Standard Deviation-SD and Coefficients of Variation-CV of sensor glucose).

## **2.2 Study design**

### *Main study*

The study will follow a randomized two-arm parallel design. Study visits will be done remotely via video calls or in-clinic when coinciding with usual care appointments. Following a baseline visit and before randomization, baseline characteristics and medical history of the participants will be collected (as detailed in section 4.3). Following randomization, the intervention group will use SNAQ app for the first 3 weeks while the control group will proceed without any modification/intervention by the study team. After the first 3 weeks, the control group will undergo 3 weeks of SNAQ app use (weeks 4-6). At the end of their respective SNAQ app periods (weeks 4-6 for the intervention group and weeks 7-9 for the control group), both groups will discontinue the use of SNAQ app for 3 weeks to assess sustainability of potential effects. Finally, both groups will be offered to use SNAQ app for 3 additional weeks as per their preference (follow-up period). The study design is illustrated in **Figure 1**.

## **2.3 Study intervention**

SNAQ is a smartphone food analysis app that estimates the macronutrient content of a meal, based on a single image. The app first determines meal content in terms of food components with input from the user to correct or add further components (e.g. foods, ingredients, sauces, herbs or seasonings). Then, the total macronutrient and energy content of the meal is determined based on the estimated volume and information from a nutritional database. Of note, the application also allows for assessing nutritional content of packaged foods by means of a barcode scanning function. The user can always adapt proposed nutritional contents at their own discretion. Meal macronutrients alongside the food pictures are collected in a detailed log which allows users to review their dietary choices. The product is not conceived by its manufacturer to be used for medical purposes and can thus not be considered a medical device.

### 3 STUDY POPULATION AND STUDY PROCEDURES

#### 3.1 Inclusion and exclusion criteria, justification of study population

Subjects fulfilling all of the following inclusion criteria are eligible for the investigation:

- Written informed consent
- Adults (aged 18 years or older)
- Type 1 diabetes (as defined by World Health Organization-WHO for at least 12 month)
- Current use of a commercial hybrid closed-loop system
- HbA1c ≤ 12% (measured within the past 3 months)
- Willing to use the SNAQ app on a daily basis for over 3 weeks
- The participant is willing to follow study specific instructions and share their treatment data with the study team

The presence of any of the following exclusion criteria will lead to the exclusion of the subject

- Any physical or psychological disease or condition likely to interfere with the normal conduct of the study and interpretation of the study results
- Previous use of SNAQ app for more than 5 days within the past 3 months
- Self-reported pregnancy, planned pregnancy within next 3 months or breast-feeding
- Severe visual impairment
- Severe hearing impairment
- Lack of reliable telephone facility for contact
- Concomitant participation in another trial that interferes with the normal conduct of the study and interpretation of the study results
- Participant not proficient in German

*Comment:*

- 1) *The exclusion of pregnant and breastfeeding participants is not due to potential safety issues but due to concerns regarding interpretation of study results (impact of pregnancy on physiology, psychometrics and behaviour patterns).*
- 2) *If the last measurement of HbA1c levels is older than 3 months, a new measurement of HbA1c will be performed if the participant consents to that, if not, the participant will be excluded.*

#### 3.2 Recruitment, screening and informed consent procedure

Participants will be recruited from the adult diabetes outpatient clinics at the University Hospital Bern or from referring clinicians working at other outpatient clinics. Potential participants will be identified by their treating clinicians. If agreed by the participants, their contact details will be shared with the research team who will approach them to provide further details about the study, both written and spoken. Specifically, the investigators will explain to each interested individual the nature of the study, its purpose, the procedures involved, the expected duration, the potential risks and benefits and any discomfort it may entail. Each participant will be informed that the participation in the study is voluntary and that he or she may withdraw from the study at any time and that withdrawal of consent will not affect his or her subsequent medical assistance and treatment. Participants will also be informed that there will be no reimbursement for the

participation in this investigation and that authorised individuals other than their treating physician may examine his/her medical records.

A study information sheet, which also contains the consent form, will be send out to the potential participants. Any questions from the subject or its related persons shall be addressed. Enough time will be given to the participant to decide whether to participate or not. Written consent will be obtained after the provision of a minimum of 24h of reflection time.

If continued interest exists and participants appear eligible, participants will be asked to sign the consent form and return it to the investigators before or on the day of the arranged baseline visit. The Sponsor-Investigator or its designate will sign the returned document before the commencement of the baseline visit and ask the participant whether a copy is desired. The participants will not be submitted to any study-related procedure before obtaining written informed consent. The signed consent form will be retained as part of the study records. The informed consent process will be documented in the patient file and any discrepancy to the process described in the protocol will be explained.

The number of approached patients who either refuse to participate in the trial or are not deemed suitable for participation by the clinical investigator will be documented with respective reason. Details will be used to create the CONSORT Flow Diagram at the end of the trial.

### 3.3 Study procedures

The study design is illustrated in Figure 1 and the schedule and details of study-related activities can be found in the Investigation Schedule (Appendix 1). To increase the convenience, all study visits can be held remotely using the Hospital's approved telemedicine channels or in-clinic visits when it coincides with the time of usual care appointments.

[figure not shown]

**Figure 1. Study Flow**

#### Baseline visit

The baseline visit will include the following procedure

- Retrieval of relevant medical information
- Questionnaire exploring the participants' current meal management practices, perceived importance and related burden
- Nutrition literacy questionnaire

In order to assess people's baseline glucose control and insulin requirements, participants will be asked to download their data from the hybrid closed-loop systems from the 14 preceding days and share them with the study team.

The following details will be recorded in the eCRF to characterize the population:

- Sociodemographic and anthropometrics variables (age, gender, body weight, height, level of education, socioeconomic status)
- Diabetes-specific medical details: age at diagnosis, duration of diabetes, type of commercial hybrid closed-loop system, type of insulin, diabetes-related complications
- Comorbidities
- Medications other than insulin (glucose lowering agents, lipid lowering agents, anti-hypertensive agents)
- History of severe hypoglycaemia and hypoglycaemia awareness status (Gold score)

All recorded parameters including units and scales are defined in the case report form.

In participants without a smartphone compatible with the newest version of SNAQ app, a study phone will be provided to the patients for the duration of the study. In addition, all participants will be provided with the premium version of SNAQ app for 12 months (including 6 weeks of the study and excluding the period when the usage of the app is not intended regarding the participation group) by using a specific code.

After completion of all baseline assessments participants will be randomized to the intervention or the control group. Participants of the intervention group will be asked to use SNAQ app for 3 weeks while in participants in the control group no instructions of any kind will be made by the study team. Before the use of the SNAQ app, participants of the intervention group will receive access to the premium version of the app using a specific code, assistance with the download of the app, registration with the assigned study ID and a short guidance through the app given by the team, using the informational material provided by SNAQ app.

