## 2 STUDY OBJECTIVES AND DESIGN

### 2.1 Hypothesis and primary objective

#### *Hypothesis*

The null hypothesis that there is no difference in the true mean time spent in the target glucose range (3.9 to 10.0mmol/L), will be tested against the alternative hypothesis that the use of the food analysis app, SNAQ, for meal management is superior to traditional meal management (two-sided alternative).

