### **Visit 1 (end of period 1)**

Visit 1 will entail the following procedures:

- Acquisition of the data download from the closed-loop system
- Acquisition of the data download from the SNAQ app (intervention group only)
- Feedback questionnaire on the SNAQ app (intervention group only)
- Nutrition literacy questionnaire (intervention and control group)

At the end of the visit and throughout Period 2, participants in the intervention group will stop using SNAQ app. To ensure that participants of the intervention group will stop using the SNAQ app, the license of the app will be temporarily de-activated remotely. Before the use of the SNAQ app, participants of the control group will receive premium version of the app for 12 months (including 6 weeks of the study and excluding the period when the usage of the app is not intended regarding the participation group) assistance with the download of the app, registration with the assigned study ID and a short guidance through the app given by the team, using the informational material provided by SNAQ app.

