# **4 STATISTICS AND METHODOLOGY**

## **4.1. Statistical analysis plan and sample size calculation**

### *Sample Size calculation*

Sample size was estimated to provide sufficient power to detect a clinically meaningful difference of 10% in the primary efficacy outcome. The sample size was calculated based on preliminary data on the efficacy of SNAQ app in improving postprandial glucose control. In data from 23 subjects (1603 meals with SNAQ app and 2018 meals without SNAQ app), mean $\pm$ SD time in target range was 85 $\pm$ 23% vs. 77 $\pm$ 35% with and without the app, respectively. Assuming a mean improvement of 10% in the intervention group with no change in the control group, and assuming

a within-participant standard deviation of 10% in both groups, a total sample size of 34 participants (17 per group) is required to achieve a power of 80% at a two-sided alpha level of 5%. Assuming a drop-out rate of 20%, we therefore aim to recruit 44 participants (22 per group).

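### Controls are not asked to refrain from private SNAQ use in Period 1, and such use would not be clearly recorded, so the primary contrast could be diluted

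*Protocol*

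**What the plan says.** - **Comparator.** The hypothesis in protocol section 2.1 is that SNAQ "for meal management is superior to traditional meal management (two-sided alternative"). The primary endpoint is measured over Day 1 to Day 21, which is Period 1.
- **Control condition.** Section 3.3 (Baseline visit) states that "in participants in the control group no instructions of any kind will be made by the study team". Section 2.2 likewise describes a control group that the study team leaves alone for the first 3 weeks.
- **Entry.** Section 3.1 excludes "Previous use of SNAQ app for more than 5 days within the past 3 months". Shorter recent use, and any amount of older use, is therefore allowed. All participants must be willing to use the app daily for a 3-week period.
- **Access.** Section 1 describes SNAQ as a publicly available app with about 2,500 users in Switzerland. Under section 3.3, controls receive the study's premium access, study-ID registration and guidance only at Visit 1.
- **Off-periods after use.** Section 3.3 (Visit 1) says: "To ensure that participants of the intervention group will stop using the SNAQ app, the license of the app will be temporarily de-activated remotely". The Visit 2 text does the same for controls in Period 3.
- **Records.** Section 3.3 takes the SNAQ download at Visit 1 from the intervention group only. Appendix 1 has a combined row for SNAQ and pump data, marked for both groups at baseline and Visit 1. The meal management questionnaire is scheduled at baseline only, and the Visit 1 feedback questionnaire goes to the intervention group only.
- **Sample size.** Section 4.1 is built on "Assuming a mean improvement of 10% in the intervention group with no change in the control group".

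**The concern.** Both the hypothesis and the sample size treat Period 1 controls as people not using SNAQ, yet the protocol rules out telling them anything. The trial is open. Controls know about the app, have said that they are willing to use it, and can obtain it themselves. A control who starts using SNAQ privately during Day 1 to Day 21 moves that group's mean towards the intervention group's mean and shrinks the estimated effect.

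Interpretation suffers as well as power. If nobody asks about use, a small or null difference could mean that the app does little or that some controls used it, and the data would offer no clear way to separate the two.

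**Working it through.** **1. Inputs from section 4.1.** Difference 10 percentage points; "a within-participant standard deviation of 10% in both groups"; two-sided alpha 5%; target power 80%; 17 evaluable per group (34 in total); 22 per group recruited (44 in total) to allow for 20% drop-out.

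**2. Reproducing the plan's figure.** Two-sample t-test with n per group, difference d and SD s: noncentrality = d / (s × √(2/n)), degrees of freedom = 2n − 2.

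- n = 17: 10 / (10 × √(2/17)) = 2.92; critical value 2.037 on 32 degrees of freedom; power 80.7%.
- n = 16: power 78.1%, so 17 is the smallest n that reaches 80%.
- Drop-out: 17 / 0.8 = 21.25, rounded up to 22 per group, 44 in total.

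The stated 34 and 44 both reproduce.

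**3. Adding private use in controls.** Let c be the share of controls who use the app in Period 1, and f the fraction of the 10-point benefit that each of them gains. The control mean then rises by c × f × 10, and the expected contrast is 10 × (1 − c × f). The SD is kept at 10. Neither c nor f is given in the documents; both are assumptions.

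| c | f | Contrast (points) | Power, 17 per group | Power, 22 per group |
|---|---|---|---|---|
| 0 | – | 10.0 | 80.7% | 90.0% |
| 10% | full | 9.0 | 72.1% | 83.0% |
| 20% | full | 8.0 | 61.9% | 73.6% |
| 30% | full | 7.0 | 50.8% | 62.1% |
| 10% | half | 9.5 | 76.6% | 86.8% |
| 20% | half | 9.0 | 72.1% | 83.0% |
| 30% | half | 8.5 | 67.1% | 78.7% |

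The last column applies if nobody drops out.

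**4. Would the use be seen?**

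- On the section 3.3 reading, no SNAQ data are taken from controls at Visit 1.
- On the Appendix 1 reading, a download may be intended for them. Controls are not registered under a study ID until that same visit, however, so earlier use under a private account would not clearly be in it.
- No questionnaire or eCRF item named in the protocol asks controls about app use after baseline.

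**The case against.** **Controls are not left without any safeguard.** A reader might infer that the protocol protects the intervention group's off-period and does nothing comparable for controls. The documents do not support that. In both cases the tool is the study licence: switched off for one group, not yet issued to the other. Section 3.3 also ties premium access to the periods in which use is intended for each group. De-activating a study licence would not block a private account in the intervention group either. This stands. What remains is private use of a public app.

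**The entry criterion is a protection.** A reader might take the 5-day allowance as a route for contamination. In fact it keeps out recent regular users, who are the likeliest to carry on, and brief use before entry is not use in Period 1. Controls are also due free access after 3 weeks, which weakens the motive to start alone. This stands and makes a high rate less plausible.

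**A hands-off control can be deliberate.** Usual care without instruction is a legitimate comparator. But section 2.1 names traditional meal management, and section 4.1 assumes no change in controls, so SNAQ non-use is part of what the trial sets out to compare. The request in section 3.3 to keep diabetes therapy stable refers to the closed-loop system and insulin, and does not mention meal apps. The participant information sheet is not available here, so whether it covers non-use cannot be judged.

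**Use might not go unnoticed.** Appendix 1 can be read as planning a SNAQ download for controls, so a flat statement that use would be invisible goes too far. The two places conflict and need reconciling.

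**The full-effect figures are a worst case.** Private users would have no study guidance and no request to use the app daily. This stands, and is why half effect is shown. The bias is towards zero and would not create a false benefit.

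**Conclusion.** The gap is real but narrow. In the one period that feeds the primary endpoint, the protocol does not ask controls to refrain from SNAQ and has no item that would clearly record private use. Any such use would bias the primary difference towards zero.

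The size is unknown. With 17 evaluable per group, use by 10% to 30% of controls would cost roughly 9 to 30 points of power at full effect and 4 to 14 points at half effect. These figures rest on an assumed rate, an assumed effect per user and an unchanged SD of 10. They are not a forecast, and nothing in the documents shows that contamination is likely or that the trial is underpowered. The sample size needs no change. This is a cheap improvement that protects the interpretation of the primary result.

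**What to change.** 1. In section 3.3, replace the no-instruction rule for controls with one request: continue usual meal management and do not use SNAQ until Visit 1. Do not bar other food apps that a participant already uses. The protocol neither excludes such users nor seeks to change their habits, and a ban would alter the comparator.
2. Add one eCRF item, for both groups at each visit, on use of SNAQ or another image-based food app in the preceding period. If the sponsor prefers to keep controls entirely uninstructed, this item alone would still make the result interpretable.
3. Reconcile section 3.3 with Appendix 1 on whether a SNAQ download is taken from controls at Visit 1.
4. Keep every participant in the randomised comparison regardless of reported use.

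Cost: one sentence in the visit script, one extra question and a slightly less hands-off control. Sample size, visits and endpoints stay as they are.

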### **Visit 1 (end of period 1)**

Visit 1 will entail the following procedures:

- Acquisition of the data download from the closed-loop system
- Acquisition of the data download from the SNAQ app (intervention group only)
- Feedback questionnaire on the SNAQ app (intervention group only)
- Nutrition literacy questionnaire (intervention and control group)

At the end of the visit and throughout Period 2, participants in the intervention group will stop using SNAQ app. To ensure that participants of the intervention group will stop using the SNAQ app, the license of the app will be temporarily de-activated remotely. Before the use of the SNAQ app, participants of the control group will receive premium version of the app for 12 months (including 6 weeks of the study and excluding the period when the usage of the app is not intended regarding the participation group) assistance with the download of the app, registration with the assigned study ID and a short guidance through the app given by the team, using the informational material provided by SNAQ app.

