#### *Further objectives*

Further objectives are to assess the sustainability of potential improvements, the usability of the food analysis app, SNAQ, as well as its impact on nutrition literacy.

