### *Nutrition literacy, meal management and feedback questionnaires*

Nutrition literacy will be expressed as mean signed and absolute relative errors (%) of carbohydrate error and be calculated over all items of the quiz on a subject level. The nutrition literacy, the meal management and the feedback questionnaire will be implemented in the survey tool of the RedCap platform and can be completed remotely using a participant specific link.

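### The Visit 1 carbohydrate quiz may be answered remotely while the intervention group's study-supplied app licence is still active, and unaided answers are not required (exploratory endpoint, low severity, cheap to fix)

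*Protocol*

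**What the plan says.** Section 2.1 names nutrition literacy among the further objectives ("as well as its impact on nutrition literacy") and lists the matching exploratory endpoint as "Carbohydrate estimation skills (absolute and relative errors from the carbohydrate quiz"). The Methods part of section 3.3 gives the scoring: "Nutrition literacy will be expressed as mean signed and absolute relative errors (%) of carbohydrate error", taken over all quiz items for each subject.

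The quiz is given at baseline and again at Visit 1, where the list of procedures reads "Nutrition literacy questionnaire (intervention and control group"). It "can be completed remotely using a participant specific link", and section 3.3 adds that "all study visits can be held remotely using the Hospital's approved telemedicine channels".

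On app access, the Visit 1 text says "At the end of the visit and throughout Period 2, participants in the intervention group will stop using SNAQ app", enforced by switching the licence off remotely. The same paragraph then describes how controls receive the premium version, help with the download and a short introduction. Appendix 1 places their SNAQ instruction at Visit 1 and lists the nutrition literacy questionnaire at the baseline visit and Visit 1 only.

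**The concern.** The quiz is meant to measure what participants can estimate for themselves. The intervention is a tool that does the same job: section 2.3 describes an app that returns the macronutrient content of a meal from one image, with user corrections and a nutritional database behind it. Section 6.2 states that it estimates carbohydrate more accurately than the average patient.

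As the Visit 1 steps are written, the quiz falls due while the intervention group's study licence is still on and before controls have theirs. Of the licences supplied by the study, only one arm's is live at that moment. If some intervention participants answer with the app open, the outcome is partly measured through the intervention. The Visit 1 comparison is the only randomised contrast for the nutrition-literacy objective.

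**Working it through.** The protocol gives no expected effect, standard deviation or sample size for this endpoint, so there is no figure to reproduce. The check is a comparison of the stated steps.

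**Order of steps at Visit 1**

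| Item | Intervention group | Control group | Source |
|---|---|---|---|
| Quiz | Due at Visit 1 | Due at Visit 1 | Section 3.3, Visit 1; Appendix 1 |
| Study-supplied licence when the quiz is due | Active since baseline; off at the end of the visit | Not yet supplied; onboarding described after the visit procedures | Section 3.3, Baseline visit and Visit 1 |
| Setting | Remote completion by link permitted | Same | Section 3.3, opening and Methods |
| Supervision, completion window or ban on aids | None stated | None stated | Whole protocol |
| Later quiz | None | None | Appendix 1 |

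**What follows**

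1. The difference in licence status when the quiz is due is created by allocation. Adjusting for the baseline quiz score cannot remove it, because at baseline neither arm holds a study licence.
2. Remote completion without an instruction leaves use of the app open. It does not show that anyone uses it.
3. For use of the app to matter, the items must be answerable with it. The protocol does not describe the items. Section 2.3 says content is computed from an estimated volume plus a database, and the accuracy statement in section 1 concerns real meals. Pictures on a screen may not be usable in that way. Entering foods by hand may help, but may leave the portion size to the participant.
4. The intervention group is off the app in Period 2. A quiz at Visit 2 would have given an app-free reading in that group, but none is scheduled.

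**Illustration only**

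Suppose there is no true learning, an unaided error *u*, an app error *e* on the quiz items, and a share *f* of the intervention group that consults the app. Then

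apparent gain = *f* × (*u* − *e*).

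Section 1 cites average errors of 20% or higher, so take *u* = 20. The documents give neither *e* nor *f*; the values below are assumptions.

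| *f* | *e* = 5 | *e* = 10 | *e* = 15 | *e* = 20 (app no help on the items) |
|---|---|---|---|---|
| 0.25 | 0.25 × 15 = 3.75 | 0.25 × 10 = 2.5 | 0.25 × 5 = 1.25 | 0 |
| 0.50 | 0.50 × 15 = 7.5 | 0.50 × 10 = 5.0 | 0.50 × 5 = 2.5 | 0 |

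The unit is percentage points of mean error. The table shows only how the result depends on two unknowns. It is not an estimate of bias in this trial, and even *u* is a literature figure rather than this quiz's error.

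**The case against.** The strongest reply is that much of this rests on what the protocol does not say. Remote completion is an option, visits involve staff contact by video or in clinic, and an instruction to answer without aids may sit in the survey itself, which is not shown. That is fair, and it limits the weight of the point. What stands is that the protocol itself fixes the sequence, with licence withdrawal at the end of the visit, and that this is the less favourable order for a test of unaided skill.

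A reader might infer that only the intervention group can look answers up. The documents do not support that. The app is on the market, with over 2,500 users in Switzerland (section 6.1), up to 5 days of use in the past 3 months does not exclude a participant (section 3.1), and websites or exchange tables are open to anyone answering by link. The arms differ in one study-supplied aid, not in access to aids altogether.

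A reader might also infer that controls who answer late, after onboarding, bias the result the other way. Nothing says that this will happen: the quiz is a visit procedure and onboarding is described after it.

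Lastly, look-up might be detectable, since the app logs meals and section 7.2 lists exported meal timing as source data. This is a partial check at best. The protocol does not say whether a query that is not saved as a meal is logged, and the Visit 2 text limits the SNAQ download to controls although Appendix 1 lists a data download for both groups.

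**Conclusion.** The point holds as a low-severity improvement, confined to the exploratory nutrition-literacy endpoint. It depends on two things that the documents leave open: whether the app can answer the quiz items, and whether participants would use it. If both hold, part of a lower intervention-group error could be look-up rather than skill, and the schedule has no app-free repeat to check against. The size cannot be derived from the documents.

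The tempting stronger conclusion is that any literacy benefit would be an artefact, or that a bias of several points should be expected. Neither follows, because that needs the assumed inputs above and carries accuracy on real meals over to an instrument that is not shown. The protocol already says of its exploratory endpoints, "so definite inferences cannot be made regarding those endpoints". That limits the consequences, though such a caveat about inference does not settle what the quiz measures. The primary and secondary endpoints come from sensor glucose and are not affected.

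**What to change.** In the Visit 1 text of section 3.3, set the order of steps:

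- Intervention group: de-activate the SNAQ licence first, then open the quiz link.
- Control group: have the quiz submitted before SNAQ download and instruction.
- Both groups, at baseline and at Visit 1: state on the quiz that answers are to be given without the app or any other aid.

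No extra visit, participant or analysis is needed. The cost is a reordering of steps that already take place around Visit 1 and one instruction line in the survey. The downside is that control onboarding starts a little later within the same visit.
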